## Abstract

**Background:**

The stomatognathic system and dysfunction in this system may be related to postural control. The proposal of the present study is to assess the effect of mandibular mobilization in individuals with temporomandibular disorder using surface electromyography of the muscles of mastication and stabilometric variables.

**Methods/Design:**

A randomized, controlled, blind, clinical trial will be carried out, with the participants divided into three groups: 1) facial massage therapy (control group), 2) nonspecific mandibular mobilization and 3) specific mandibular mobilization. All groups will be assessed before and after treatment using the Research Diagnostic Criteria for Temporomandibular Disorders, surface electromyography of the masseter and temporal muscles and stabilometry. This study is registered with the Brazilian Registry of Clinical Trials (RBR9x8ssz).

**Discussion:**

A large number of studies have employed surface electromyography to investigate the function/dysfunction of the muscles of mastication and associations with signs and symptoms of temporomandibular disorders. However, it has not yet been determined whether stabilometric variables offer adequate reliability in patients with this disorder. The results of the proposed study will help determine whether specific and/or nonspecific mandibular mobilization exerts an effect on the muscles of mastication and postural control. Moreover, if an effect is detected, the methodology defined in the proposed study will allow identifying whether the effect is local (found only in the muscles of mastication), global (found only in postural control) or generalized.

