Studies have suggested that massaging the muscles of mastication, joint mobilization, manual therapy, mandibular exercises, biofeedback and the application of electrophysical resources may be effective in the treatment of TMD [22-26]. Joint mobilization has proven effective at reducing pain, disability and local ischemia [27], breaking fibrous adhesions, enhancing the extensibility of non-contractile structures, increasing the range of motion, enhancing the transmission of afferent information through the stimulation of mechanoreceptors and stimulating proprioception and the production of synovial fluid [27,28]. The use of joint mobilization has been tested on individuals with TMD, in whom a reduction in pain and increased mandibular range of movement (ROM) have been reported [29-32].

Massage has proven effective at diminishing EMG activity and pain [19,21], preventing the formation of connective tissue adherences, enhancing the production and circulation of endogenous opioids [19], increasing local blood flow, facilitating the elimination of residual substances and extracellular fluid, improving the nutrition of myofibrils and promoting relaxation and a sensation of wellbeing [33,34]. Massaging the muscles of mastication has been administered to patients with TMD, leading to a reduction in pain, an increase in mandibular ROM and a decrease in EMG activity in the muscles [21,35].

Postural control may be related to afferent signals of the trigeminal nerve, which depend on information from receptors of the stomatognathic complex (dentoalveolar ligaments, muscle and joint receptors). Moreover, TMD may alter muscle activity and the positioning of structures of the stomatognathic system, interfering in the information transmitted for the control of posture. Thus, relaxation of the muscles of mastication (as assessed through surface EMG) and the alignment of joint structures (assessed through a clinical exam) may alter afference from the receptors of the stomatognathic system, thereby affecting postural control (assessed through stabilometry). Based on this hypothesis, the aim of the proposed study is to determine the effect of facial massage and mandibular mobilization on EMG activity of the muscles of mastication and static balance in individuals with TMD.

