## Methods/Design

### Overview of research design

A randomized, controlled, blind, clinical trial is proposed to study the effects of specific and nonspecific mandibular mobilization. The participants will be allocated to three groups through a randomization process using opaque envelopes. Each group will receive a specific form of treatment for TMD. The control group (CG) will receive massage therapy and those submitted to joint mobilization will be divided into two groups: the specific mobilization group (SMG) and the nonspecific mobilization group (NMG). Evaluations will be carried out before and after treatment using the Research Diagnostic Criteria for Temporomandibular Disorders (RDC/TMD), EMG of the masseter and temporal muscles and stabilometry.

After screening, individuals with TMD (based on the RDC/TMD) will be selected. The study will be divided into three types of treatment, three evaluations and two phases, to which all individuals will be submitted:

Evaluation 1: randomization of treatment with allocation to treatment groups, stabilometric analysis and EMG analysis, with the administration of the protocol for the respective treatment.

Evaluation 2: second stabilometric and EMG evaluation immediately following respective treatment.

Treatment phase: treatment following respective protocol.

Evaluation 3: third stabilometric and EMG evaluation and second administration of the RDC/TMD questionnaire.

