The weakest index regarding reliability was the SaEn, followed by sway area. The variation in ICC among poor, fair and good and the high SEM demonstrate that these variables should not be considered when investigating the possible effects of mandibular mobilization for the treatment of TMD.

The results of this pilot studied showed that mean velocity was the most reliable measure, which is consistent with earlier reports, and can be selected as a reliable postural sway measure. Moreover, the results of the proposed study will help determine whether specific and/or nonspecific mandibular mobilization exerts an effect on the muscles of mastication and postural control. Moreover, if an effect is detected, the methodology defined in the proposed study will allow identifying whether the effect is local (found only in the muscles of mastication), global (found only in postural control) or generalized.

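### The objective asks whether mobilization has an effect, but the only comparator is active massage: the randomized contrast is mobilization versus massage, and the within-group tests have no control

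*Protocol article*

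**What the plan says.** The Abstract (Methods/Design) lists three arms: "1) facial massage therapy (control group), 2) nonspecific mandibular mobilization and 3) specific mandibular mobilization". There is no sham, untreated or waiting-list arm. The Overview of research design confirms that "The control group (CG) will receive massage therapy" and also states that "Each group will receive a specific form of treatment for TMD".

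The Background treats massage as active on the trial's own outcome: "Massage has proven effective at diminishing EMG activity and pain". For patients with TMD it reports massage of the muscles of mastication as "leading to a reduction in pain, an increase in mandibular ROM and a decrease in EMG activity in the muscles". It then makes massage part of the question: "the aim of the proposed study is to determine the effect of facial massage and mandibular mobilization on EMG activity".

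Elsewhere the question narrows to mobilization alone. The Abstract (Discussion) says the results will "help determine whether specific and/or nonspecific mandibular mobilization exerts an effect on the muscles of mastication and postural control". The closing paragraph of the main Discussion repeats this, and that section opens by giving the effect of mobilization as the main objective. Both places add a labelling rule. An effect seen in the muscles of mastication alone is local, one seen in postural control alone is global, and otherwise it is generalized.

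Data analysis plans intra-group tests (repeated-measures ANOVA or Friedman) and inter-group tests (one-way ANOVA or Kruskal-Wallis). It does not say which of them answers the objective.

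**The concern.** The arm called control is also one of the treatments under study, and the protocol expects it to move the EMG outcome. Neither planned type of test estimates the effect named in the objective:

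- The inter-group contrast is mobilization minus massage. It understates any mobilization effect that massage shares.
- The intra-group change is treatment plus natural course, regression to the mean and the effect of repeat testing. No arm allows these to be separated.

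The headline conclusion is at stake, and with it the local, global or generalized label. That label depends on an effect being present in one system and absent in the other, so it needs a valid reading of a null result. This design gives none unless the reading is confined to differences from massage.

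**Working it through.** **1. What each test estimates.** Write M for the mean effect of mobilization on an outcome, S for that of massage, and B for background change (natural course, regression to the mean, repeat testing) common to all arms.

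- Intra-group change, mobilization arm: M + B
- Intra-group change, massage arm: S + B
- Inter-group difference in change: (M + B) − (S + B) = M − S

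The objective asks about M, and none of the three quantities equals it. If S is zero or in the beneficial direction, a difference favouring mobilization implies that M is beneficial. If M − S is near zero, M = S = 0 and M = S ≠ 0 look the same.

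**2. The labelling rule on each basis.**

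- *Inter-group basis.* Suppose mobilization acts on both systems, and massage matches it on EMG but does nothing for balance. The EMG contrast is null and the balance contrast is not. The effect is labelled global when it is generalized.
- *Intra-group basis.* Suppose M = 0 on both outcomes and B ≠ 0 on both. Both before-after tests can be significant, and the effect is labelled generalized when there is none.

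**3. The plan's own figure.** Inputs from Pilot studies, pilot study 1 (eight women, before and after five sessions of nonspecific mobilization): T0 = 1.19, T1 = 1.08, SD = 0.14, power 0.80. The change is 1.19 − 1.08 = 0.11, and 0.11/0.14 = 0.79 SD. Alpha is not stated; I assume 0.05 two-sided, and take 0.14 as the SD of the change.

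n = [SD × (1.96 + 0.84)/change]² = [0.14 × 2.80/0.11]² = 12.7, rounded up to 13.

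This reproduces the stated 13 as a single-group before-after calculation. A two-arm comparison on the same inputs needs 2 × 12.7 = 25.4, so 26 per arm. The stated number was therefore built on uncontrolled change.

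**4. Size on the between-arm contrast.** Assumptions: 13 per arm (the protocol does not say whether 13 is per group or in total; this is the favourable reading), SD 0.14, two-sided 0.05, normal approximation, no multiplicity correction. The massage fractions are assumptions, since the protocol gives no figure.

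Power = Φ(difference/[0.14 × √(2/13)] − 1.96)

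| Massage change as share of 0.11 (assumed) | Between-arm difference | In SD units | Power at 13 per arm | Needed per arm for 80% |
|---|---|---|---|---|
| 0% | 0.11 | 0.79 | 52% | 26 |
| 50% | 0.055 | 0.39 | 17% | 102 |
| 100% | 0 | 0 | see step 5 | none suffices |

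**5. Equal change in every arm.** In 20,000 simulated trials with three arms of 13, each with mean change 0.11 and SD 0.14, one-way ANOVA of the change was significant in 5.3%, the false-positive rate. The before-after t-test within an arm was significant in 74%. Those results would be the same whether the 0.11 was all treatment or all background change.

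**The case against.** An active comparator is a legitimate design, and the article is open about using one. Both points stand. The defect is the mismatch between the comparator and the stated inference, not the choice of massage.

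A reader might infer that the trial cannot show any effect of mobilization. The documents do not support that. Superiority over a massage arm would support an effect, assuming massage does no harm, and the article claims only to help determine the answer. What cannot be read is a null or equal result.

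A reader might also infer that equal improvement in all arms would be reported as no effect of mobilization. No section says how a null between-group result will be read. The intra-group tests would show equal improvement, and the Background includes the effect of massage in the aim. With those tests planned, the likelier error is the opposite one: crediting uncontrolled before-after change to treatment.

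Three limits on the argument also stand:

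- The Background reports massage effects on EMG, pain and range of movement. For balance it offers only a hypothesis through altered afference, so the problem is firmest for EMG.
- The pilot change was measured at maximum intercuspation. The Background does not say under which condition massage lowered EMG, so massage's effect on this exact measure is not documented.
- The 0.11 is itself an uncontrolled change in eight women, and the protocol does not say whether 0.14 is the SD of the change or of single values.

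These limits affect the figures and leave the mismatch in place. An analysis plan kept elsewhere would not cure it either, because the published objective and labelling rule are worded wrongly for this design.

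**Conclusion.** The point holds as a mismatch between objective and design. The trial can answer whether specific or nonspecific mobilization changes EMG and postural sway more or less than massage. It cannot attribute a before-after change within any arm to the treatment given, and a null contrast does not distinguish two effective treatments from two ineffective ones. The local, global or generalized label can be wrong on either basis while the plan is followed exactly.

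The figures are illustrative. They rest on 13 per arm, alpha 0.05 two-sided, SD 0.14 for change, and assumed shares of the pilot change for massage. On those terms a pairwise between-arm comparison has about 52% power if massage does nothing and about 17% if it gives half the change. A significant within-arm result is likely (about 74%) whenever the change is 0.11, whatever its cause. The mismatch itself needs none of these assumptions; it follows from the arms and the stated aims.

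**What to change.** 1. In the Abstract (Discussion), the aim at the end of the Background, and the opening and closing objective statements of the main Discussion, state the question as whether specific or nonspecific mobilization changes EMG and CoP mean velocity more or less than facial massage.
2. In Data analysis, name the between-arm comparison of change as the basis for inference, and label within-arm change, massage included, as descriptive.
3. State that a null contrast is reported as no difference from massage shown, with its confidence interval.
4. Apply the local, global or generalized label only to differences from massage, and do not treat a non-significant contrast as absence of effect in that system.

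The cost is wording and a more modest claim. Arms, visits and recruitment do not change, and the trial is listed as still recruiting. Rewording does not raise the power of the between-arm contrast, so the confidence interval in item 3 has to carry that uncertainty.

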## Background

Correlations between dental occlusion and bodily balance have recently been analyzed [1-4]. The possibility of an association between conditions affecting the stomatognathic system, such as temporomandibular disorder (TMD), and postural problems have also been investigated [1,5-8]. Deviations in global posture lead to bodily adaptations and realignments, which can affect the organization and function of the temporomandibular joint (TMJ) [9]. Moreover, the effect of alterations in the muscles of mastication and dentoalveolar ligaments on the stomatognathic system can lead to a perturbation of visual stabilization, generating postural imbalance [2].

Constant oscillations (body sway) occur to maintain balance. Afferent (sensory) signals originate from proprioceptive, tactile, vestibular and visual receptors. Proprioception of the mandibular system emerges from the muscles of mastication (due to changes in the mandible position), receptors of the TMJ (due to rotation and/or translation of the condyles) and dentoalveolar ligaments (due to changes in occlusal contacts) and is determined by the trigeminal nerve [1,2,10-13].

Contact between the jaws is maintained by ligaments and muscles, including the masseter and temporal muscles. When these muscles are in tonic equilibrium, the mandible is at rest [2,14]. This mandibular resting position can be altered by different circumstances, such as occlusal interferences, TMD, the position of the head and body and emotional tension [14]. Electromyography (EMG) has evidenced a relationship between the stomatognathic system and cervical spine and how head movements [15], changes in body posture [14], occlusal contact pattern and the vertical dimension of the teeth [15-18] can alter EMG activity in the muscles of mastication and affect the mandibular resting position. Indeed, EMG activity in the muscles of mastication at rest in individuals with TMD may be greater than that found in individuals without this disorder, indicating muscle hyperactivity [19-21].

Studies have suggested that massaging the muscles of mastication, joint mobilization, manual therapy, mandibular exercises, biofeedback and the application of electrophysical resources may be effective in the treatment of TMD [22-26]. Joint mobilization has proven effective at reducing pain, disability and local ischemia [27], breaking fibrous adhesions, enhancing the extensibility of non-contractile structures, increasing the range of motion, enhancing the transmission of afferent information through the stimulation of mechanoreceptors and stimulating proprioception and the production of synovial fluid [27,28]. The use of joint mobilization has been tested on individuals with TMD, in whom a reduction in pain and increased mandibular range of movement (ROM) have been reported [29-32].

Massage has proven effective at diminishing EMG activity and pain [19,21], preventing the formation of connective tissue adherences, enhancing the production and circulation of endogenous opioids [19], increasing local blood flow, facilitating the elimination of residual substances and extracellular fluid, improving the nutrition of myofibrils and promoting relaxation and a sensation of wellbeing [33,34]. Massaging the muscles of mastication has been administered to patients with TMD, leading to a reduction in pain, an increase in mandibular ROM and a decrease in EMG activity in the muscles [21,35].

Postural control may be related to afferent signals of the trigeminal nerve, which depend on information from receptors of the stomatognathic complex (dentoalveolar ligaments, muscle and joint receptors). Moreover, TMD may alter muscle activity and the positioning of structures of the stomatognathic system, interfering in the information transmitted for the control of posture. Thus, relaxation of the muscles of mastication (as assessed through surface EMG) and the alignment of joint structures (assessed through a clinical exam) may alter afference from the receptors of the stomatognathic system, thereby affecting postural control (assessed through stabilometry). Based on this hypothesis, the aim of the proposed study is to determine the effect of facial massage and mandibular mobilization on EMG activity of the muscles of mastication and static balance in individuals with TMD.

## Methods/Design

### Overview of research design

A randomized, controlled, blind, clinical trial is proposed to study the effects of specific and nonspecific mandibular mobilization. The participants will be allocated to three groups through a randomization process using opaque envelopes. Each group will receive a specific form of treatment for TMD. The control group (CG) will receive massage therapy and those submitted to joint mobilization will be divided into two groups: the specific mobilization group (SMG) and the nonspecific mobilization group (NMG). Evaluations will be carried out before and after treatment using the Research Diagnostic Criteria for Temporomandibular Disorders (RDC/TMD), EMG of the masseter and temporal muscles and stabilometry.

After screening, individuals with TMD (based on the RDC/TMD) will be selected. The study will be divided into three types of treatment, three evaluations and two phases, to which all individuals will be submitted:

Evaluation 1: randomization of treatment with allocation to treatment groups, stabilometric analysis and EMG analysis, with the administration of the protocol for the respective treatment.

Evaluation 2: second stabilometric and EMG evaluation immediately following respective treatment.

Treatment phase: treatment following respective protocol.

Evaluation 3: third stabilometric and EMG evaluation and second administration of the RDC/TMD questionnaire.

### Flowchart (Figure 1)

**Figure 1 F1:**
[figure not shown]
Method flowchart.

#### ***Blinding***

Participants will be blinded to the group allocation and will not be aware if they are being subjects of the treatment or control groups. The therapists will not be blinded because they will perform the interventional protocols. However, the therapists will not take part in the outcome measurements or the statistical analyses, and will be requested not to disclose details about their treatment to the outcome assessors or participants. The outcome assessors will be blinded to the randomization allocation and will not be involved in performance of the interventions. The statistician will be blinded to the group allocation until completion of the statistical analyses.

#### ***Inclusion criteria***

A diagnosis of TMD, complete dentition (except third molars) and mandibular deviation and/or deflection.

#### ***Exclusion criteria***

Crossbite, open bite, mandibular prognathism or retrognathism, denture use, current orthodontic or physiotherapeutic treatment, neurological disorder that may affect balance, use of orthopedic insoles.

### Ethical considerations

The proposed study received approval from the local Human Research Ethics Committee under process number 457625 dated 28 September 2011. The study will be conducted in compliance with the norms that regulate research involving human subjects contained in Resolution number 196/97 of the Brazilian National Health Council and is registered with the Brazilian Registry of Clinical Trials (RBR9x8ssz). All participants will be informed regarding the objectives and procedures of the study and will be asked to sign a statement of informed consent agreeing to participate.

### Procedures

#### ***Research diagnostic criteria for temporomandibular disorders - RDC/TMD***

The RDC/TMD is a biaxial diagnostic tool [36] composed of a clinical exam based on a detailed physical evaluation of the mouth opening pattern, vertical extension of mandibular movement, noises in the TMJ upon palpation during vertical movement, excursive mandibular movements and noises in the TMJ upon palpation during lateral excursion and protrusion. The clinical diagnosis is divided into three categories [37,38] (Table 1). The RDC/TMD questionnaire is made up of 31 items addressing general health, oral health, history of facial pain, mouth opening limitation, joint noises, habits, bite, ringing in the ears, health conditions in general, joint problems, headache, current behavior and social and economic profile.

**Table 1 T1:** Classification and diagnosis of temporomandibular disorder (TMD) subgroups based on Research Diagnostic Criteria for Temporomandibular Disorder (RDC/TMD)

**Group**	**Subgroup**
I	A. myofascial pain
	B. myofascial pain with limited opening
	No group I diagnosis
II right	A. disk displacement with reduction
	B. disk displacement without reduction with limited opening
	C. disk displacement without reduction without limited opening
	No group II diagnosis
II left	A. disk displacement with reduction
	B. disk displacement without reduction with limited opening
	C. disk displacement without reduction without limited opening
	No group II diagnosis
III right	A. arthralgia
	B. osteoarthitis of TMJ
	C. osteoarthosis of TMJ
	No group III diagnosis
III left	A. arthralgia
	B. osteoarthitis of TMJ
	C. osteoarthosis of TMJ
	No group III diagnosis

